### Participants and selection criteria

The population will include 177 participants (men and women) with the diagnosis of MI according to criteria of “Third Universal definition of myocardial infarction” and clinical classification of MI type 1, called “Spontaneous myocardial infarction” [1], recruited from the cardiology services by the physician specialists. In turn, before testing protocol begins, an ergometry is performed according to the clinical history for participants’ screening to ensure there is no ongoing myocardial ischemia. After completion of the informed consent process, clinical history, blood sample for baseline analysis, electrocardiogram, and echocardiogram are obtained from all participants to evaluate the eligibility criteria. Only participants who have been managed with revascularization are included. The inclusion and exclusion criteria for the INTERFARCT study are shown in Table 1. After assessment for eligibility and consent, different clinical research members collect the baseline data necessary to complete the pre-randomization information.

**Table 1 Tab1:** Inclusion and exclusion criteria for the INTERFARCT study

Inclusion criteria
- MI type I: Spontaneous MI [1], with and without ST elevation
- Effective revascularization treatment (coronary artery bypass grafting or percutaneous coronary intervention)
- Age ≥ 18 years, clinically stable on sinus rhythm
- Between six months and two years after the MI
- Left ventricular ejection fraction > 50%
- Time availability (45 min, two days a week for 16 weeks) to carry out the exercise program
Exclusion criteria
- Unstable coronary artery disease, uncontrolled hypertension, malignant ventricular arrhythmia, atrial fibrillation, exercise-induced ischemia, and ventricular failure during exercise
- Other significant medical conditions including, but not limited to: chronic or recurrent respiratory, gastrointestinal, neuromuscular, neurological, or psychiatric conditions; musculoskeletal problems interfering with exercise; severe kidney disease (creatinine clearance < 30 mL/min, calculated in accordance with Modification of Diet in Renal Disease equation [MDRD]), autoimmune or collagen vascular diseases; immunodeficiency diseases or a positive human immunodeficiency virus test; anemia (hemoglobin < 12 g/dL), bleeding disorders, chronic thrombotic disorders, or hypercoagulable states; malignancies in the past five years, with the exception of skin cancer therapeutically controlled; endocrine and metabolic disorders, including type 1 diabetes; moderate to severe peripheral artery disease (> IIa in Fontaine’s classification); any other medical condition or disease that is life-threatening or that can interfere with or be aggravated by exercise
- Any other co-morbidity with life expectancy < 1 year
- Could not perform a valid baseline exercise test - Obesity > 35 kg/m^2^
- Pregnancy or breastfeeding
- Plans to be out of the city > 2 weeks

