
On the other hand, the relevance of overall high-quality food patterns, rather than focus on single nutrients and foods, has emerged as a powerful paradigm to address the diet and to assess their potential cardiovascular disease preventative effects [21]. The Mediterranean diet (Mediet), representing the dietary pattern usually consumed among the populations bordering the Mediterranean Sea, has been widely reported to be a model of healthy eating for its contribution to a favorable health status and a better quality of life, reducing overall mortality from cardiovascular diseases [22].

Considering all the above-mentioned points, the INTERFARCT study is designed to investigate what effect different 16-week supervised aerobic INTERval exercise programs (HV vs LV) with Mediet recommendations will have in people after suffering an acute myocardial inFARCTion compared to AC that is recommended a Mediet and physical activity without supervision sessions.

We hypothesize that: (1) supervised HIIT will get superior improvements in cardiovascular health than only physical activity recommendations; and (2) a high-intensity and LV exercise program will get similar results compared to a high-intensity and HV exercise program. Therefore, the primary objective of this randomized controlled trial (RCT) will be to assess the effects of different programs of HIIT and Mediet recommendations on overall health, cardiorespiratory fitness, biomarkers, ventricular function, and perception of quality of life after MI compared to only physical activity recommendations. The secondary objectives will be: (1) to analyze the differences in the studied variables between the two HIIT programs (HV vs LV) with Mediet recommendations to observe the effect of exercise volume; and (2) to analyze whether a treatment with only recommendations (exercise and diet) is effective in the secondary prevention of cardiovascular disease compared to supervised exercise.

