### Exercise intervention program

The participants in the HIIT groups will exercise two non-consecutive days per week for 16 weeks under supervision by an exercise specialist and we will also request to continue with their normal activity patterns outside of the study protocol. All the exercises sessions will start and finish with BP monitoring; training intensity will be controlled by HR monitoring (Polar Electro, Kempele, Finland) and through the rate of perceived exertion using the Borg’s original scale (6–20 points). Each session will include a 10-min warm-up with joint mobility (i.e. starting at the top of the body and working the way down, from the neck, shoulders, upper back, hips, and ankles) with continuous leg movement to facilitate the venous return and coordination exercises (e.g. toe-tapping arm circles, heel walks, high knee walk, backwards high knee skip) and a 10-min cool-down period with passive stretching exercises on the floor to ensure a progressive return to the resting values of both HR and BP. The main portion of the training session will consist of aerobic exercises (i.e. one day of the week on the treadmill and the second one on the bike) developing progressively both the volume (i.e. 20 min to 40 min in HV-HIIT, whereas in LV-HIIT the duration will always be 20 min) and intensity. The rationale of mixing bike and treadmill will be to avoid the osteoarticular impact of two treadmill days taking into account the HIIT program. Intensity will be individually tailored to HR at moderate or vigorous intensities, adjusting the speed and incline of the treadmill or the power and speed on the bike to achieve the planned target HR (Table 2). The importance of targeting moderate and high intensity will be emphasized.

**Table 2 Tab2:** Intervention program for high-volume high-intensity (HV-HIIT) and low-volume high-intensity (LV-HIIT) groups on the treadmill and the bike. Volume and intensity progression

	High-intensity interval		Moderate-intensity interval		High-intensity interval		Moderate-intensity interval	
	HV-HIIT treadmill				LV-HIIT treadmill			
Weeks	Volume (min)	Intensity (%HRres)	Volume (min)	Intensity (%HRres)	Volume (min)	Intensity (%HRres)	Volume (min)	Intensity (%HRres)
1–2	8	85	12	65	8	85	12	65
3–4	12	85	13	65	8	85	12	65
5–6	16	90	14	70	8	90	12	70
7–8	16	90	19	70	8	90	12	70
9–10	16	95	24	75	8	95	12	75
11–12	16	95	24	75	8	95	12	75
13–16	16	95	24	75	8	95	12	75
	HV-HIIT bike				LV-HIIT bike			

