#### High-intensity interval training protocol on the treadmill

The high intensity aerobic exercise groups will carry out a 5- to 10-min warm-up period at a moderate-intensity (i.e. HR values between VT1 and VT2 or 65–75% of HR reserve) on the treadmill, before walking two intervals of 4 min at high intensity (i.e. HR values up to VT2 to peak intensity or ≥ 85% to < 95% of HR reserve). The participants will exercise at the lower-intensity limit for the first two weeks of the training period before increasing the intensity towards the upper limit. Between the high-intensity intervals, 3 min of walking at moderate intensity will be conducted. The training session will end with a 4-min cool-down period at moderate intensity. This is a traditional protocol in cardiac rehabilitation programs and research with cardiac patients [15, 45]. This will give a total exercise time of 20 min. While this protocol will be kept in the LV-HIIT group, every two weeks the HV-HIIT will progress to four intervals of 4 min at high intensity and 40 min of total volume (Table 2).

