#### High-intensity interval training protocol on the bike

The high-intensity aerobic exercise groups will carry out a 5- to 10-min warm-up period on the bike. After that, the participant will cycle for 30 s at high intensity (i.e. HR values up to VT2 to peak intensity or ≥ 85% to < 95% of HR reserve) followed by 60 s at moderate intensity (i.e. HR values between VT1 and VT2 or 65–75% of HR reserve) [46]. Four repetitions (1 rep = 30 s high intensity followed by 60 s moderate intensity) will be initially performed in both groups and gradually increased to 16 repetitions in the HV group, while eight repetitions will be completed (Table 2) in the LV group. The training session will end with a 4- to 7-min cool-down period at moderate intensity. The protocol design for biking has already been established in cardiac rehabilitation programs [14].

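### The 45-minute availability criterion is too short for a full HV-HIIT session in weeks 5–16 (about 50–60 min, 24 of 32 sessions), while LV-HIIT sessions fit it

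*Protocol article*

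**What the plan says.** Among the inclusion criteria in Table 1 is "Time availability (45 min, two days a week for 16 weeks) to carry out the exercise program".

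The section Exercise intervention program describes the session in three parts. First: "Each session will include a 10-min warm-up with joint mobility". Last: "a 10-min cool-down period with passive stretching exercises on the floor". The main portion between them is aerobic work on the treadmill one day and the bike the other, lasting "20 min to 40 min in HV-HIIT, whereas in LV-HIIT the duration will always be 20 min". Blood pressure is also checked at the start and finish of each session; no duration is given.

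Table 2 lists the high- and moderate-intensity minutes of the main portion by arm, machine and week. The treadmill section says that "every two weeks the HV-HIIT will progress to four intervals of 4 min at high intensity and 40 min of total volume". The bike section has repetitions "gradually increased to 16 repetitions in the HV group, while eight repetitions will be completed" in the LV group.

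The first secondary objective compares the two HIIT programs "with Mediet recommendations to observe the effect of exercise volume".

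**The concern.** The availability line screens people before they are randomised, so it has to cover the longest session of whichever arm they may enter. If it covers LV-HIIT but not HV-HIIT, someone with 45 free minutes is eligible, can complete every LV session and cannot complete most full HV sessions.

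Any shortening for that reason would fall on HV only. It would narrow the difference in volume that the first secondary objective sets out to study. The second hypothesis in the Background expects LV and HV to give similar results, so a narrower delivered contrast would tend towards the hypothesised answer.

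**Working it through.** **Inputs.** Availability 45 min (Table 1). Warm-up 10 min and cool-down 10 min per session, two sessions a week for 16 weeks = 32 sessions (Exercise intervention program). Main portion = high + moderate minutes (Table 2).

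**The plan's own figure.** The HV treadmill rows give 8+12 = 20, 12+13 = 25, 16+14 = 30, 16+19 = 35 and 16+24 = 40 min. LV treadmill gives 8+12 = 20 min. This reproduces the stated 20 to 40 min for HV and 20 min for LV. The bike rows agree to within half a minute.

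**Full session = 10 + main portion + 10.**

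| Weeks | HV main | HV session | LV session | HV sessions over 45 min |
|---|---|---|---|---|
| 1–2 | 20 | 40 | 40 | 0 of 4 |
| 3–4 | 25 | 45 | 40 | 0 of 4 |
| 5–6 | 30 | 50 | 40 | 4 of 4 |
| 7–8 | 35 | 55 | 40 | 4 of 4 |
| 9–16 | 40 | 60 | 40 | 16 of 16 |

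Totals over 45 min: HV 24 of 32, LV 0 of 32. Blood pressure checks come on top.

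**Could the two 10-minute parts already be inside the main portion?** No.

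- The treadmill section has its own on-machine warm-up and cool-down, and these are inside the 20 min: 5 + 4 + 3 + 4 + 4 = 20. Table 2's 12 moderate minutes equal 5 + 3 + 4. They are moderate-intensity treadmill work, not joint mobility or floor stretching.
- There is no room for another 20 min. "Between the high-intensity intervals, 3 min of walking at moderate intensity will be conducted", so four intervals take 4×4 + 3×3 = 25 min. The HV treadmill portion leaves 30−25 = 5, 35−25 = 10 and 40−25 = 15 min in weeks 5–6, 7–8 and 9–16.
- At its longest, the HV bike core is 16 × 1.5 = 24 min, leaving 40−24 = 16 min.
- Table 2 assigns these remaining minutes to moderate work at 70–75% of HR reserve.

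If only one 10-minute part counted, weeks 9–16 would still take 50 min, so 16 of 32 HV sessions would exceed 45 min.

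**Size for one person held to exactly 45 min.** Planned aerobic minutes:

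- HV: 4×20 + 4×25 + 4×30 + 4×35 + 16×40 = 1080.
- LV: 32×20 = 640.
- Planned contrast: 1080 − 640 = 440. Half-minute bike differences alter the HV total by at most 12×0.5 = 6 and the LV total by at most 4×0.5 = 2.

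| What such a person keeps | HV main limited to | HV total | Contrast | Lost |
|---|---|---|---|---|
| Both 10-min parts | 25 | 4×20 + 28×25 = 780 | 140 | 300 |
| One part | 35 | 80+100+120+140+16×35 = 1000 | 360 | 80 |
| Neither | 45 (not binding) | 1080 | 440 | 0 |

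These figures leave no time for blood pressure checks.

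**The case against.** **The 45 min may mean aerobic time only.** The abstract labels the arms by 40 and 20 min, and Table 2 lists only those minutes. On that reading 45 covers the 40-minute maximum. The reading is possible, but Table 1 speaks of carrying out the exercise program without that restriction, and the program's own section puts the warm-up and cool-down in each session.

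**No harm is shown.** Sessions are supervised and prescribed by Table 2, 45 min is a minimum, and nothing in the article says a session may be cut at 45 min. This stands. A reader might infer that the HV-versus-LV result is biased, or that HV will lose more people under the 80% compliance rule. The article gives no number of time-limited participants and no shortened sessions, so neither can be concluded.

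**Only moderate work would be lost.** A reader might note that the 25-minute interval core just fits the 25 min left, and infer that the high-intensity contrast would survive intact. The article does not support this. With the on-treadmill warm-up (at least 5 min) and 4-minute cool-down, four intervals need 5 + 25 + 4 = 34 min, and even three need 5 + 18 + 4 = 27. No split into preserved high-intensity and lost moderate minutes can be claimed.

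**LV might not always fit.** At the upper ends of the on-machine ranges, an LV treadmill session is 10+4+3+4+4 = 25 min, or 45 with both 10-minute parts, and an LV bike session is 10+12+7 = 29, or 49. But Table 2 and the session text fix LV at 20 min, so this qualifies the LV figure without overturning it. It does show that the article's minute accounting is approximate: the 30 min in HV weeks 5–6 is also below the 34 just derived.

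**Conclusion.** The point holds as a mismatch between a screening criterion and the session it screens for. By the article's own minutes, 24 of 32 full HV-HIIT sessions exceed 45 min, by 5 to 15 min before blood pressure checks, and no LV-HIIT session does. This rests on taking the 45 min as the whole session and on the Table 2 totals.

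The consequence for the HV-versus-LV objective is a possibility. It ranges from 0 to 300 of 440 contrast minutes for a person held to exactly 45 min, and how many such people there are is unknown. The primary comparison of HIIT with AC is not shown to be affected. Priority is low.

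**What to change.** For anyone still to be enrolled, change the Table 1 line to at least 60 min plus time for blood pressure monitoring, two days a week for 16 weeks. A bare 60 min would leave no time for those checks beside a 60-minute HV session.

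For participants already enrolled, report delivered aerobic minutes by arm beside the HV-versus-LV result, so that readers can see whether the planned contrast was achieved.

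The cost is one line in Table 1 and one descriptive summary. A few time-limited people would become ineligible. Trial status says recruitment is finishing, so the eligibility change will reach few people, and the report of delivered minutes is the part that remains useful.

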### Measurements

The measurements used in the protocol will be taken before and after the intervention period (16 weeks). The study protocol flow of participants is outlined in Fig. 1. The post-intervention test will be scheduled the following week after finishing the 16-week intervention period. The primary outcome variable is cardiorespiratory fitness, measured through VO_2peak_. The secondary outcome variables include left ventricular function, body composition, biochemical profile, vascular endothelial function, dietary adherence, the state of depression and anxiety, and health-related quality of life. The SPIRIT figure showing the respective time points for assessments and intervention is provided in Fig. 2.

**Fig. 1 Fig1:**
[figure not shown]
Planned *flow diagram* of the INTERFARCT study from recruitment to the end of the intervention

**Fig. 2 Fig2:**
[figure not shown]
SPIRIT *figure* showing an overview of the assessment schedule at baseline and follow-up in the INTERFARCT study. IPAQ International Physical Activity Questionnaire, ECG electrocardiogram, MSWT Modified Shuttle Walking Test, CPET cardiopulmonary exercise test

#### Anthropometry and body composition

Anthropometry includes stature (SECA 213), total body mass (SECA 869), BMI calculated as (total body mass [kg]/stature [m^2^]), and waist and hip circumferences (SECA 200) to calculate waist:hip ratio. All measurements will be taken in accordance with guidelines from the International Society for the Advancement of Kinanthropometry [24]. Furthermore, fat-free mass, total body water, and fat mass will be estimated with bioelectrical impedance analysis (Tanita, BF 350 and Tanita, BC-418 MA).

#### Lifestyle and health behavior

Participants’ health-related quality of life will be determined using the 36-item Short Form Medical Outcome Questionnaire (SF-36) [25]. It is a 36-item questionnaire that measures eight multi-item dimensions of health: physical functioning; social functioning; role limitations due to physical problems; role limitations due to emotional problems; mental health; energy/vitality; body pain; and general health perception. Scores will be coded, summed, and converted into a scale from 0 (worst possible health state) to 100 (best possible health state) for each dimension item.

Anxiety and depression levels will be assessed through the Spanish version of the Hospital Anxiety and Depression Scale (HADS), which is a 14-item self-report screening scale. The HADS consists of a seven-item anxiety subscale and a seven-item depression subscale. Each item scores on a 4-point Likert scale [26].

#### Cardiovascular measurements at rest

A 12-lead electrocardiogram, left ventricular function by echocardiography, flow-mediated dilation (FMD), and carotid intimae media thickness (CIMT) by ultrasound scanning will be the methods used to assess central and peripheral cardiovascular variables.

Echocardiography will be performed by two experienced cardiologists blinded to the participant’s group assignment. The average of these two measurements will be used in the statistical analysis [27]. Participants will be examined at rest using an ultrasound system (GE Healthcare, Vivid 9) according to standard procedures for evaluated left ventricle dimensions and diastolic and systolic functions [27]. Left ventricle end-diastolic diameter, diastolic and systolic volumes, and ventricular mass will be measured and indexed to body surface area. Assessment of left ventricle diastolic function will include peak early (E) and late (A) diastolic mitral inflow velocities, early deceleration time (EDT), early diastolic tissue Doppler velocity (e’), and E/e’ ratio. On the other hand, determination of left ventricle systolic function will be carried out by calculation of biplane ejection fraction (Simpson’s rule), cardiac output (CO), and determination of peak annulus velocity in systole (S′).

For each participant, microvascular and conduit artery function in the forearm will be assessed with non-invasive, high-resolution ultrasonography of the brachial artery, using a handheld ultrasound probe. Flow-mediated dilation, a biomarker for endothelial function, will be evaluated with high-resolution ultrasonography and performed following the International Brachial Artery Reactivity Task Force guidelines using a 2.5- to 13-MHz linear array transducer (GE Healthcare, Vivid 7) with a stereotactic probe-holding device. Conduit artery function will be assessed of FMD (endothelium-dependent response) and nitroglycerin-mediated dilation (endothelium-independent response) [28–30].

Carotid intima-media thickness (GE Healthcare, Vivid 7) will be carried out by two sonographers blinded to the intervention’s groups assignment. For each individual, mean CIMT will be defined as the average of all six segments intima-media thickness measurements in each carotid artery [31, 32]. The image analyses will be performed with validated software (eTRACK) [33] and all ultrasonographic measures will be analyzed by another blind specialist.

#### Physical fitness

Physical fitness will include the Modified Shuttle Walking Test (MSWT) and a peak, symptom-limited cardiopulmonary exercise test (CPET). The two tests will be conducted on different days. The purpose of doing a CPET and MSWT will be to evaluate the exercise responses in both physical activity modalities (i.e. walking/running and biking).

The MSWT requires the participant to walk up and down a 10-m course and it will be performed as previously described by Singh et al. [34]. Participants will walk along a flat, indoor 10-m course marked by two cones placed 0.5 m in from each end of the course. A shuttle will refer to one 10-m lap. Standardized prerecorded instructions for the test will be played from a digital recording immediately before beginning the test. The test will be externally paced, with signal beeps at regular intervals to indicate when the participant should be turning around the cone to commence the next shuttle. A triple beep will signal the next level and an increase in walking speed. Participants will commence the test at a walking speed of 0.5 m/s (level 1), allowing the participant 20 s to complete each of the three shuttles in level 1. There will be a speed increment of 0.17 m/s each minute for a maximum of 15 min. The test will be stopped when the participant can no longer maintain the required pace or is > 0.5 m from the cone before the signal beep after one opportunity to catch up or if the test is completed. Additional criteria for early termination of the test will include patient distress, dizziness, angina, or onset of severe musculoskeletal pain, failure of the heart rate (HR) to increase with exercise or attainment of 85% of the maximum HR (estimation by subtracting the person’s age from 220). The number of shuttles completed will be recorded at the completion of each test and converted to the distance walked. Before commencing the test, with the participant in a seated position, baseline HR and BP will be recorded. HR and Borg scale (scale of 6–20) will be monitored throughout the test; BP and HR continue to be recorded a further 5 min after completion of the test [35, 36].

The CPET will be performed in the upright position on an electronically braked Lode Excalibur Sport Cycle Ergometer (Groningen, The Netherlands). Testing protocol will start at 0 W with gradual increments of 10 W every minute to exhaustion with continuous ECG monitoring. The test will not be preceded by any type of warm-up and the participant will cycle at least 70 rpm. The expired gas analysis will be conducted using a commercially available system (Ergo CardMedi-soft S.S, Belgium Ref. USM001 V1.0) that will be calibrated before each test session with a standard gas of known concentration and volume. Breath-by-breath gas exchange data will be measured continuously during exercise and averaged every 60 s. Peak oxygen uptake will be defined as the highest oxygen uptake (VO_2peak_) value attained toward the end of the test. Achievement of true peak effort will be assumed in the presence of two or more of the following criteria: (1) volitional fatigue (> 18 on the BORG scale); (2) peak respiratory exchange ratio (VCO_2_/VO_2_) ≥ 1.1; (3) achieving > 85% of age-predicted HR_max_; and (4) failure of VO_2_ and/or HR to increase with further increases in work rate [9]. A self-reported Borg rating of perceived exertion (scale of 6–20) will be recorded at the end of each stage. BP will be measured every 2 min throughout the test. Ventilatory thresholds (i.e. VT1 and VT2) will be assessed by standardized methods using the V-slope and ventilatory equivalents. The first ventilatory threshold (VT1) will be identified as the point of transition in the carbon dioxide production (VCO_2_) vs VO_2_ slope from < 1 to > 1, or VT1 will also be identified as the nadir of the ventilatory equivalent (VE) of VO_2_ vs work rate relationship. The second ventilatory threshold (VT2) will be identifiable as the nadir of the VE/VCO_2_ vs work rate relationship. [9] After completion of the test, participants will remain on the bike for a further 5 min for recovery with an electrocardiogram (ECG) and BP monitoring. Absolute and relative indications for terminating the exercise test will be taken into account [37]. The identification of the two VT will determine the three different exercise intensity domains or ranges for exercise design (R1, R2, R3): (R1) light to moderate exercise intensity with HR values below VT1; (R2) moderate to high or vigorous exercise intensity with HR values between VT1 and VT2; and (R3) high to severe exercise intensity with HR values up to VT2 to peak intensity. When it is not possible to identify the VT2, exercise intensity domains will be established taking into account percentages of HR reserve, i.e. moderate intensity is defined as 65–75% of HR reserve, high intensity from ≥ 85% to < 95% of HR reserve [9].
